#### Compulsive Exercise Test

CE is measured by the Compulsive Exercise Test (CET),^39^ which is composed of 24 items with 5 subscales: avoidance and rule driven behaviour, weight control exercise, mood improvement, lack of exercise enjoyment, and exercise rigidity (eg, ‘I exercise to burn calories and lose weight’). For CLIMB, only the subscales avoidance and rule-driven behaviour and weight control exercise will be included in the analysis since they are deemed the most relevant in athletes and have been reported to have adequate validity (factor analysis) and internal consistency (weight control exercise: a=0.82, avoidance and rule-driven behaviour: a=0.87).^40^

#### The Body Shape Questionnaire short version

The Body Shape Questionnaire short version (BSQ-8C)^41^ is used to measure body dissatisfaction among participants (eg, ‘Have you felt so bad about your shape that you have cried?’). This short 8-question version is derived from the original 34-item BSQ, and it is shown to be reliable and valid.^42^ We use the Swedish BSQ-8C which has been found to exhibit high internal consistency (α=0.94) as well as excellent test–retest properties.^43^

#### Depression Anxiety and Stress Scale

Mental health problems are measured by the Depression Anxiety and Stress Scale.^44^ The 21 items consider the week prior to answering the survey and observe symptoms related to depression, anxiety and stress (eg, depression: ‘I felt that I had nothing to look forward to’; anxiety: ‘I was aware of dryness of my mouth’; stress: ‘I found it difficult to relax’). The cut-off scores group participants into groups showing normal, mild, moderate, severe or extremely severe symptoms. The exact cut-off values differ in each of the three categories. It is the most widely used version of the survey and boasts test–retest and an internal consistency of α=0.81–0.96.^44 45^

#### Pittsburgh Sleep Quality Index

Sleep quality is measured by the Pittsburgh Sleep Quality Index (PSQI),^46^ which includes 19 items and evaluates 7 subcategories: Subjective sleep quality, sleep latency, sleep duration, habitual sleep efficiency, sleep disturbances, use of sleeping medications and daytime dysfunction (eg, ‘During the past month, how often have you had trouble sleeping because you… wake up in the middle of the night or early morning’) . A Global Score is composed of these categories on a scale of 0–21, where ‘0’ indicates no sleep difficulty and ‘21’ indicates severe difficulties in all areas. The PSQI has shown adequate internal consistency, reliability and construct validity. Cronbach’s alphas have been reported to 0.80 across groups and correlations between global and component scores have been shown to be moderate to high.^46^

Symptoms of RED-S will be measured by Edlund Health Q, a 15-item Swedish survey focusing on menstrual cycles, injury and eating habits.

Physical activity and sedentary behaviour are measured by two indicator questions established by the Swedish National Board of Health and Welfare (Socialstyrelsen).^47^ The first item is regarding the amount of high intensity activity measured in time per week, such as cardiovascular training. The second item asks the amount of low intensity activity measured in time per week, such as walking or gardening. These two questions are only answered by the control group to establish eligibility among the participants.

DEXA will be used for measuring bone mineral density.^48^ This non-invasive imaging technology uses a small amount of ionising radiation to quantify the amount of bone, fat and lean tissue, granting the examiners the opportunity to assess the risk of fracture as well as form an overall perception of the bone’s objective health and nutritional status.

The web-based questionnaire first introduces the purpose, aims and ethics of CLIMB, emphasising the anonymity of the participant. If the participant is <15 years of age, consent from both guardians is required. The questionnaire will be answered by all participants at baseline (rock climbers and controls), but the follow-up questionnaires will only be completed by the climbing group. This is to facilitate future data collection and analysis, as the control group data will only be analysed at baseline as part of a cross-sectional study. The follow-up measurements are, therefore, only required from the rock climbers in order to provide longitudinal patterns. DEXA will only be performed on rock climbers at baseline.

### Statistical methods

#### Sample size

No previous data on injury incidence based on overuse injuries exist for rock climbers. Based on previous retrospective data from rock climbers,^49^ using a power of 80%, a significance level of 5% and an expected relative risk of 1.5 for the primary outcome, we calculated that approximately 55 participants were needed in each group (rock climbers and control group).

### Main exposure variables

DE behaviour, body image, overuse injuries/injuries, indicators of LEA, mental health problems, compulsive training, perfectionism, sleep quality, sedentary behaviour and bone density.

### Outcome

The outcome ED will be measured with the EDE-Q. The EDE-Q consist of four subscales, restrained eating, eating concern, shape concern and weight concern addressing core dimensions of EDs. A score of >4 is indicative of an ED, and for the present study a score of >2.5 will be used as an indication of subclinical eating disturbances. Thus, higher scores are indicative of more severe symptoms of ED pathology.

Our primary outcomes are EDs symptoms measured with EDE-Q and overuse injuries measures with OSTRC-O. Our secondary outcomes are bone density (DEXA), symptoms of RED-S (Edlund Health Q), mental health problems (Depression, Anxiety and Stress Scale), sleep quality (PSQI), perfectionism (FMPS), CET and body dissatisfaction (BSQ-8).

### Data analysis plan

Multinominal logistic regression analyses will be used to determine the associations between each of the exposures and trajectories of outcomes. The associations as ORs and 95% CIs will be reported. Bivariate models to measure the crude associations between the exposures and trajectories will be built.

The differences between the rock climbers and controls regarding the above-mentioned outcome measure ED will be analysed using multivariate analysis of variance (MANOVA). Both within-group and between-group analysis will be conducted. Further analyses among rock climbers with high ED versus low ED will be compared in relation to bone density, injuries, mental health and symptoms of RED-S. The MANOVA will be used for that purpose. A one-way repeated measures ANOVA will be used to identify changes over the 2-year span in the two groups of rock climbers with high ED versus low ED. In cases where overall significant changes are detected, post hoc analysis will be applied to specify where the between-group differences exist.

Structural equation modelling will be used at a later stage to investigate if the variables body image, injuries, mental illness, sports environment, bone density (from baseline) and EDs can predict injuries.

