**Method and analysis:**

This prospective longitudinal study aims to recruit Swedish competitive rock climbers (>13 years) via the Swedish Climbing Federation. A non-athlete control group will be recruited via social media (n=equal of the climbing group). Data will be collected using streamlined validated web-based questionnaires with three follow-ups over 2 years. Inclusion criteria for rock climbers will be a minimum advanced level according to International Rock-Climbing Research Association. The non-athlete control group is matched for age and gender. Exclusion criteria are having competed at an elite level in any sport as well as training more often than twice per week. Statistical analyses will include multinominal logistic regression, multivariate analysis of variance (MANOVA) and structural equation modelling (SEM). We will assess effect measure modification when relevant and conduct sensitivity analyses to assess the impact of lost to follow-up.

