**Trial registration number:**

NCT05587270.

STRENGTHS AND LIMITATIONS OF THIS STUDYLongitudinal assessment of disturbed eating, mental health status, overuse injuries, bone health and symptoms indicative of relative energy deficiency in advanced rock-rock climbers and normal controls.The use of valid and reliable instruments and measurement methods and the large number of potential confounders will improve the internal validity of the estimated associations.The use of dual-energy X-ray absorptiometry complements the participant’s self-report data with objective measurements on bone health.Multivariate statistical analysis will be executed to answer the research questions.One limitation is the use of self-report questionnaires only rather than the combination of self-report and structured interviews.

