### Instruments

The first portion of the questionnaire aims to confirm that participants are eligible for inclusion, with a climbing level of advanced or above as classified by IRCRA. Demographic data will be gathered and reported including factors such as age, time practising the sport, amount of weekly training hours, climbing level and gender. Symptoms related to eating disturbances, RED-S, body image, compulsive training, perfectionism, mental health problems, sleep quality, overuse injuries and menstrual dysfunction will thereafter be measured (see table 1).

**Table 1 T1:** Measurements in the CLIMB-study.

Variable	Instrument	Baseline	Follow-up (6 months, 1, 2, 3 and 5 years postbaseline)
Eating disorder symptoms	The Eating Disorders Questionnaire (Fairburn and Beglin, 1994)^33^	X	X
Overuse injuries	The Oslo Sports Trauma Research Centre Overuse Injury Questionnaire (Clarsen *et al*, 2013)^35^	X	X
Perfectionism	The Frost Multidimensional Perfectionism Scale (Frost *et al)*^36^	X	X
Compulsive training	The Compulsive Exercise Test (Taranis *et al*)^39^	X	X
Body dissatisfaction	Body Shape Questionnaire, brief version (Welch *et al*)^41^	X	X
Mental health	Depression Anxiety Stress Scale-21 (Lovibond and Lovibond)^44^	X	X
Sleep quality	The Pittsburg Sleep Quality Index (Carpenter and Andrykowski)^46^	X	X
Symptoms of relative energy deficiency	Relative Energy Deficiency in Sports: RED-S (Edlund Health Q, Edlund, 2020)^50^	X	X
Physical activity and sedentary behaviour	Indicator Questions from the Swedish National Board of Health and Welfare	X*	
Bone density	DEXA	X†	

*Physical activity and sedentary behaviour will only be performed on the control group.

†DEXA will only be performed on a proportion of rock climbers.

DEXA, dual-energy X-ray absorptiometry.

In addition to the web-based questionnaire, bone health using dual-energy X-ray absorptiometry (DEXA) will be measured for climbing participants at baseline.

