## Discussion

Climbing is a weight sensitive sport where athletes generally benefit from a lean body shape and low weight^6^—a risk factor for eating disturbances. There are very few studies regarding eating disturbances among rock climbers. A study by Joubert *et al*, examining DE among international sport lead rock climbers, displayed that 6.3% of male and 16.5% of female climbers had DE.^30^ Similarly, a study examining amenorrhoea among female competitive climbers showed that 15.8% of female climbers had amenorrhoea. The IFSC recently released a statement to counteract this development of the sport. Due to the over-representation of eating disturbances reported in other lean sports and the poor treatment prognosis, early detection and prevention of eating disturbances and energy deficiency is essential, especially considering the growing popularity of the sport.

There are several major strengths of CLIMB. The first is the use of longitudinal data within several domains related to disturbed eating and mental health issues by using validated questionnaires, reducing misclassification of outcomes. The few studies published at this time, on this topic, do not consider multiple mental health parameters that CLIMB intends to address, such as perfectionism, sleep habits, body dissatisfaction and CE. It is the first study on rock climbers which also includes a control group, providing vital context on disease prevalence. CLIMB will be representative of the advanced climbing community at large in Sweden as it includes a wide age span of both genders who climb at advanced and elite levels around Sweden, markedly decreasing the risk of selection bias. Additionally, this large sample of climbers contributes to ensuring external validity. The use of DEXA complements the participant’s self-report data with objective measurements on the effects that relative energy deficiency is associated with, establishing a point of action and initiative to prevent and treat afflicted athletes.

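### The only model form stated for the exposure–trajectory odds ratios is crude, so as written they are not protected against confounding, most clearly by gender

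*Protocol article*

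**What the plan says.** The Data analysis plan gives the trajectory analysis three sentences. The method is "Multinominal logistic regression analyses will be used to determine the associations between each of the exposures and trajectories of outcomes". The effect measure follows: "The associations as ORs and 95% CIs will be reported". The third sentence is the only one about how models are built: "Bivariate models to measure the crude associations between the exposures and trajectories will be built". No covariates, adjustment set or rule for selecting confounders is given for these odds ratios there or elsewhere in the article.

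The strengths box says that, together with valid instruments, "the large number of potential confounders will improve the internal validity of the estimated associations". The Instruments section lists the demographic data to be collected: "factors such as age, time practising the sport, amount of weekly training hours, climbing level and gender". The abstract adds one further commitment on modelling: "We will assess effect measure modification when relevant and conduct sensitivity analyses to assess the impact of lost to follow-up".

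**The concern.** This is an observational study, and its Introduction says that work identifying risk and prognostic factors is needed to develop prevention. Odds ratios linking exposures such as body image, compulsive training or mental health to symptom trajectories will be read in that light. A crude odds ratio cannot separate an exposure that acts on the outcome from one that is simply more common in women or in elite climbers. Measured confounders improve validity only if the analysis uses them, and the one model form named does not. The claim in the strengths box and the analysis as stated therefore do not fit together.

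**Working it through.** **Is the gap filled elsewhere in the article?**

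- *Matching.* Age and gender matching applies to the control group. Controls answer at baseline only (Study design and participants), so matching cannot protect a trajectory analysis within climbers.
- *Effect modification and loss-to-follow-up analyses* (abstract). Neither is confounder adjustment.
- *MANOVA and repeated-measures ANOVA* (Data analysis plan). These are separate analyses, and no covariates are named.
- *Structural equation model* (Data analysis plan). It is deferred to a later stage, predicts injuries rather than trajectories, and does not list age, gender or climbing level.

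**Which confounders does the article itself support?**

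- *Gender.* The Discussion reports that "6.3% of male and 16.5% of female climbers had DE". The odds ratio for women against men is (0.165/0.835) / (0.063/0.937) = 0.1976/0.0672 = 2.94. The Introduction also says that physical ideals affect girls more strongly than boys, which ties gender to body image, a listed exposure. That link gives direction only.
- *Climbing level.* The main hypothesis expects more symptoms in elite than in advanced climbers. This is a stated hypothesis, not data.
- *Age.* Support is indirect: the Introduction mentions a national federation's age limits, set to reduce risk. Eligibility starts at 13.

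**How large could confounding by gender be?** The plan gives no figure of its own on this point, so this is an illustration.

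Inputs from the Discussion: risk of disordered eating p_m = 0.063 in men and p_f = 0.165 in women. Assumptions: share of women w = 0.5; no exposure effect within gender; exposure prevalence e_m = 0.20 in men and e_f = 0.30 to 0.60 in women. Disordered eating stands in for one trajectory class against a reference class.

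Collapsing over gender:

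- exposed cases: a = w·e_f·p_f + (1−w)·e_m·p_m
- exposed non-cases: b = w·e_f·(1−p_f) + (1−w)·e_m·(1−p_m)
- unexposed cases: c = w·(1−e_f)·p_f + (1−w)·(1−e_m)·p_m
- unexposed non-cases: d = w·(1−e_f)·(1−p_f) + (1−w)·(1−e_m)·(1−p_m)
- crude OR = ad/(bc)

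For e_f = 0.60: a = 0.0495 + 0.0063 = 0.0558; b = 0.2505 + 0.0937 = 0.3442; c = 0.0330 + 0.0252 = 0.0582; d = 0.1670 + 0.3748 = 0.5418. OR = (0.0558 × 0.5418)/(0.3442 × 0.0582) = 0.03023/0.02003 = 1.51.

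| Prevalence, men | Prevalence, women | True OR within gender | Crude OR |
|---|---|---|---|
| 20% | 20% | 1.00 | 1.00 |
| 20% | 30% | 1.00 | 1.14 |
| 20% | 40% | 1.00 | 1.26 |
| 20% | 50% | 1.00 | 1.38 |
| 20% | 60% | 1.00 | 1.51 |

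The 20%/60% case gives 1.55 with 30% women and 1.34 with 70% women. A milder imbalance of 40%/60% gives 1.22 with 50% women and 1.16 with 70% women.

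**The case against.** The strongest reply is that the article does not say crude models are the only ones. The sentence on multinomial regression is silent on adjustment, the word crude usually implies an adjusted counterpart, and the strengths box suggests one was intended. A journal article condenses the full protocol, and the covariate set is commonly left to that document or the SAP. Part of this stands: an adjusted step may well have been intended, and the article does not rule it out. But the article goes beyond silence. It names a crude step, names no other, and claims a benefit that the named step cannot deliver.

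A reader might infer that the reported odds ratios will be confounded by gender, age and climbing level. The documents do not support that. Data tie only gender to the outcome; level rests on a hypothesis and age on indirect evidence. The article gives no exposure prevalences by gender, and without imbalance there is no bias from gender.

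Gender is also partly in view. The Introduction plans to examine gender differences, and effect modification may be assessed. Gender-specific estimates, if produced, would remove confounding by gender, but neither statement commits to them for these odds ratios.

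The illustration has limits, which stand. The 6.3% and 16.5% come from an external sample of international lead climbers and describe a binary outcome, not trajectories. The value 1.51 needs a threefold imbalance in the exposure.

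**Conclusion.** The point holds in this form: the article states only a crude model for the exposure–trajectory odds ratios, nothing else in it adjusts them, and this sits badly with the claim that measured confounders improve validity. The odds ratios are unprotected against confounding, most clearly by gender and, on the study's own hypothesis, by climbing level. Under the stated assumptions a null exposure would show a crude odds ratio of 1.14 to 1.51, and 1.00 with equal prevalence. These figures show what is possible; they do not estimate the bias in this study, whose size and direction cannot be derived from the article. The matter should be settled before the trajectory analyses, but it is a correction to the stated analysis, not a flaw in the design or the data collected.

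**What to change.** In the Data analysis plan, state that the primary reported association for each exposure comes from a multinomial logistic model adjusted for gender, age and climbing level (advanced or elite), with the crude odds ratio shown beside it for comparison. All three variables are already collected at baseline, so the change is one sentence and no new data.

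Keep the set this small. Each covariate costs one parameter per non-reference trajectory class: three single-term covariates add 3 × (K − 1) parameters for K classes, so 6 if K = 3 and 9 if K = 4. (The article does not give K.) Cases may be few. With the planned 55 or so climbers, half of them women, the Discussion's rates imply 55 × (0.063 + 0.165)/2 = 6.3 with disordered eating. More may enrol, since the whole eligible population is invited.

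Two tempting extensions are best avoided. Weekly training hours should not be a routine covariate: they overlap with the compulsive-training exposure and may lie on the pathway to overuse injury, so adjusting could remove real effect. Nor should the trajectory outcome be replaced by a continuous EDE-Q score, which would change the planned outcome and do nothing for the other primary outcome, overuse injuries on the OSTRC-O.

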Our main hypothesis is that elite and advanced rock climbers will present more DE symptoms compared with controls, with elite rock climbers showing more symptoms than advanced rock climbers. A secondary hypothesis is that rock climbers who report more eating disturbances will present with higher levels of health problems including decreased bone density, CE, depression, body dissatisfaction, menstrual disturbances and more overuse injuries as compared with rock climbers with less symptoms of eating disturbances, as these secondary variables are correlates of EDs.^32^ We expect these patterns to be stable over time. The authors will also examine the gender differences in these categories and expect, for example, to find higher percentages of DE among women than men, following the pattern of the presented literature. At the time of writing, there exists sparse research on the connection between rock climbing, DE and energy deficiency. The presented hypotheses are therefore largely grounded on findings in other sports with similar bodily and/or weight requirements, such as ballet, figure skating and gymnastics. Due to the rapidly increasing popularity of recreational and competitive climbing, longitudinal cohort studies are, therefore, urgently needed to understand the aetiology of health problems related to EDs in rock climbers in particular. Studies that identify risk and prognostic factors are required to develop health promotion and disease prevention strategies, which ultimately can reduce the burden of disease in rock climbers worldwide.

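### The high- versus low-ED comparison among climbers leaves out compulsive exercise and body dissatisfaction, two outcomes that the secondary hypothesis names

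*Protocol article*

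**What the plan says.** The last paragraph of the Introduction states a secondary hypothesis about climbers only. Those who report more eating disturbance should present with more "health problems including decreased bone density, CE, depression, body dissatisfaction, menstrual disturbances and more overuse injuries as compared with rock climbers" who have fewer such symptoms.

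The Data analysis plan then describes the corresponding contrast, with RED-S as the last item of its list: "Further analyses among rock climbers with high ED versus low ED will be compared in relation to bone density, injuries, mental health and symptoms of". On the method, the plan states: "The MANOVA will be used for that purpose". The list of outcomes has no wording that leaves it open.

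The Outcome section counts among the secondary outcomes "sleep quality (PSQI), perfectionism (FMPS), CET and body dissatisfaction (BSQ-8". Table 1 marks the CET and the Body Shape Questionnaire for baseline and for all follow-ups. The Compulsive Exercise Test section says which two of the five CET subscales will be analysed: avoidance and rule-driven behaviour, and weight control exercise.

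**The concern.** The hypothesis and the analysis meant to test it carry different outcome lists. Two outcomes that the authors expect to be worse in the high-ED group do not appear in the one sentence that says what the two groups will be compared on. The data are collected and both measures are declared secondary outcomes, so neither lack of data nor a change of scope explains the gap.

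At stake is whether the plan tests what it hypothesises. An analyst who follows the text would report the MANOVA without either outcome. One who follows the Introduction would add both. Because a MANOVA returns a joint verdict on the variables put into it, the two analysts would be testing different statements under the same name.

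**Working it through.** No figure in the article bears on this point, so the check sets the two lists side by side and then asks whether another planned analysis fills the gap.

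**Step 1: match the lists.**

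| Named in the secondary hypothesis | In the high- versus low-ED MANOVA? |
|---|---|
| Bone density | Yes |
| Overuse injuries | Yes, listed as injuries |
| Depression | Not by name; falls under mental health |
| Menstrual disturbances | Not by name; falls under RED-S symptoms |
| Compulsive exercise | No |
| Body dissatisfaction | No |

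Of 6 named outcomes, 2 match, 2 are reachable through a wider heading, and 2 are absent (2 + 2 + 2 = 6).

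**Step 2: the two reachable outcomes.** Mental health is measured by the DASS, whose items "observe symptoms related to depression, anxiety and stress", with separate cut-offs for each of the three. RED-S symptoms come from the Edlund Health Q, "a 15-item Swedish survey focusing on menstrual cycles, injury and eating habits". Both hypothesised constructs can therefore be recovered from a subscale or from items. The article does not say which scores enter the model.

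**Step 3: other analyses that might supply the two absent outcomes.**

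- *Multinomial regression.* It relates each exposure to trajectories of outcomes. Disordered eating behaviour heads the exposure list, and CET and BSQ-8 are secondary outcomes, so a model of their trajectories on disordered eating is possible. Compulsive training and body image are also on the exposure list, so they may equally enter as predictors. The article does not say which outcomes will have trajectories. In either case the result is an odds ratio for trajectory membership, not a difference in level between the two ED groups.
- *Repeated-measures ANOVA.* It names the high- and low-ED groups and looks for change over 2 years, but names no outcome.
- *Structural equation model.* Body image is a predictor of injuries; compulsive exercise is not mentioned.

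None of the three clearly gives the contrast that the hypothesis describes. The MANOVA includes bone density, which is measured at baseline only, so the contrast in question is in effect a baseline one.

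**Step 4: can the absent outcomes simply be appended?** The CET subscales and the BSQ-8C are self-report scores asked of all climbers, so they can be. The existing list has a separate difficulty that shows up once it is aligned with the hypothesis. A joint MANOVA on complete cases keeps only participants with every variable. Menstrual items exist for women only, and the Table 1 footnote limits DEXA to a proportion of climbers. Putting all six outcomes into one model would exclude men and every climber without a scan.

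**The case against.** The strongest reply is that these outcomes are not left out of the study. Disordered eating is a listed exposure and CET and BSQ-8 are listed outcomes, so on a natural reading their association is planned in the trajectory models, in the hypothesised direction. The repeated-measures ANOVA also names the two ED groups and does not restrict the outcomes. The hypothesis introduces its list as examples, not as a fixed set. This stands in part: it would be wrong to say that no planned analysis could touch these variables, or that the MANOVA is the only analysis of the two groups. It does not remove the mismatch. A list of examples still names the two outcomes, and the sentence that specifies the comparison leaves them out.

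A second reply concerns depression and menstrual disturbance. A reader might infer that the plan has replaced them with broader composites. The documents do not support that: no DASS total and no RED-S composite score is specified, the DASS subscales can enter a MANOVA as separate variables, and the choice of subscale is a detail that a condensed article may leave to the full plan.

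A third reply is that BSQ-8C overlaps in content with the EDE-Q shape and weight concern subscales, so a difference between ED groups on it is partly built in. This stands as a caution on interpretation. It is not a reason to omit an outcome that the authors themselves hypothesise.

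**Conclusion.** The point holds, at minor severity. Two of the six outcomes named in the secondary hypothesis, compulsive exercise and body dissatisfaction, have no place in the comparison written to test it. The trajectory models may bear on them but do not clearly replace it. The primary outcomes, the sample size and the significance level are untouched.

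A reader might go further and infer that the omission costs power or raises the false-positive rate. The article gives no expected differences or correlations for these outcomes and no expected size of the high-ED group, so any power contrast would come from the effects one chose to assume. A shorter list does not in itself add multiplicity.

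The conclusion assumes that the list in the Data analysis plan is meant as written, and that high and low ED will be defined from the EDE-Q, the instrument that the article names for ED. The second assumption matters only for the caution about content overlap.

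**What to change.** In the Data analysis plan, make the list for the high- versus low-ED comparison agree with the secondary hypothesis:

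- Add the two CET subscales already chosen for analysis, and the BSQ-8C.
- Say that the DASS depression subscale serves the depression part of the hypothesis and the menstrual items of the Edlund Health Q the menstrual part.
- Analyse the menstrual items separately in women and bone density separately in the climbers who had a DEXA scan, so that the joint MANOVA does not drop men or climbers without a scan.
- Note in the interpretation that BSQ-8C shares content with the EDE-Q shape and weight concern subscales that help to define the groups.

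The cost is wording. Every variable is already collected, and no visit or instrument is added. The downside is a slightly larger outcome family: three scores are added (two CET subscales and one BSQ-8C score), and two outcomes are tested outside the joint model. The Study status section describes the baseline analyses as still to come; the list should be settled before they are run, or the additions labelled as such if they have been.
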